If the arrhythmia onset time is not clear due to mild or non-existent symptoms and the time from arrhythmia onset to CV cannot be determined unequivocally the patient is not eligible for participation regardless of anticoagulation status. Haemodynamically unstable patients, as well as those with other major complicating acute illnesses, are excluded from the study. If randomized to acute CV group, the procedure must be performed within 48 h of arrhythmia onset. Subjects must be suitable for discharge from the ED despite the treatment group. Furthermore, if rate control strategy is decided instead of acute rhythm control in the ED as a first-line treatment strategy, the patient is not eligible.

The treating physician in the ED always has the final authority to determine the patient’s eligibility for the study and remains responsible for the patient’s care. Eligible and willing patients are required to give informed consent which is received by study personnel trained in the protocol.

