### Patient management in both groups

All patients visit cardiological outpatient clinic within 5–9 days after discharge from ED where their clinical condition and treatment is revised according to contemporary ESC guidelines.^9^ All patients are interviewed by a research nurse and a cardiologist to verify their prevalent health status. Briefly, all major contributing conditions for AF/AFL are screened for, and treatment strategy (rhythm or rate control and anticoagulation therapy) is revised if needed. Anamnestic information of possible shorter arrhythmia episodes not leading to healthcare visits and subsequent documentation are also recorded. Symptom severity is characterized using the European Heart Rhythm Association (EHRA) symptom scale^23^ and a standardized questionnaire covering several different aspects of AF-related symptoms.^24^ Relevant comorbidities, like obstructive sleep apnoea, are also screened using required additional diagnostics. Comprehensive transthoracic echocardiogram is performed for all subjects at the outpatient visit. Data on laboratory values, including additional relevant measurements such as thyroid hormone levels if not obtained during the ED visit, are collected. Information on CV procedures—including the number of prior CVs, methods used, success rates, and complications—is also recorded. If more aggressive rhythm control therapies are needed (antiarrhythmic medication by flecainide, amiodarone or dronedarone, or catheter ablation), initiation of the therapy is withheld for the first month to ensure unbiased estimate of rhythm status during the follow-up time. However, if aggressive rhythm control is indicated due to e.g. unbearable symptoms caused by repeatedly reoccurring atrial fibrillation or flutter paroxysm with the need for more than three CVs before the end of the first month after the outpatient clinic visit, it is allowed for in the protocol. If rate control is preferred as treatment strategy (patient asymptomatic), this will be implemented thereafter.

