In the elective group, CV is performed during the visit to restore sinus rhythm if AF or AFL has not converted spontaneously by that time. Adequate protection against cardioembolic events is ensured by verifying that therapeutic anticoagulation has been maintained for at least 3 weeks prior to CV, or by TEE if adequate prior anticoagulation is not ensured^9^ (an option the patients are informed before enrollment). TEE prior to delayed CV in patients without adequate prior anticoagulation was incorporated into the protocol to ensure patient safety and to allow accurate assessment of the primary and secondary endpoints. If a thrombus is found in TEE, CV is delayed for at least 3 weeks to ensure adequate anticoagulation, and a new TEE is performed before CV to ensure resolution of the thrombus. The decision of long-term anticoagulation is made according to the ESC guidelines.^9^ Method of CV is selected by the treating cardiologist. If the first method fails (for example pharmacological CV), another can be adopted.

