### Data collection and follow-up

Each patient completes a form requesting full disclosure of medical status and history in the ED, and this information is verified using electronic health records and written medical records which cover all prior specialized healthcare visits and the patients’ current medications. Furthermore, ED data on patient status (including haemodynamic parameters and laboratory values), received medical treatments and additional diagnostics are also collected.

After the outpatient clinic visit, a standard 12-lead ECG is recorded for all patients after 4 weeks (closest working day) from cardiology outpatient clinic visit. The date for this ECG is predefined so that the rhythm status is measured as it is at that date. In addition, patients are asked to fill in a symptom severity questionnaire also disclosing possible shorter arrhythmia episodes (not captured by ECG recordings) occurring during this time. A standard 12-lead ECG is also repeatedly recorded 3 months after the outpatient clinic.

All patient health records, and the Finnish Care Register for Healthcare are reviewed 1 and 3 months after the outpatient visit, as well as at 1 and 5 years after enrollment. Data on especially subsequent visits to ED due to AF/AFL and all other visits to specialized healthcare including major adverse cardiac and cerebrovascular events are recorded.

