### Primary and secondary end-points

The primary end-point in this study is the presence of sinus rhythm verified by ECG on a predefined date 4 weeks after the visit to the outpatient clinic. The primary analysis will follow the intention-to-treat principle, comparing randomized groups irrespective of spontaneous conversion or expedited CV in the delayed group. A per-protocol analysis will be conducted as a sensitivity analysis in accordance with recommendations for non-inferiority trials.^25^ Early unplanned CV (0–4 days after ED visit) due to unbearable symptoms in the delayed rhythm control strategy is considered a prespecified intercurrent event and leads to exclusion from the per-protocol analysis. This exclusion is performed to study the non-inferiority of successfully delaying the CV by at least 5 days from presentation to ED. Patients with missing end-point data are excluded from the analyses, and the number of patients with missing data is reported. Secondary end-points include the overall recurrence of AF or AFL, the number of required CVs and duration of ED stay, the need to use antiarrhythmic drugs within the first month, unplanned CV rate within the first week due to unbearable symptoms (elective approach), cardiovascular events—including events monitored for safety, and quality of life. The details of the end-points are listed in *Table 2*.

**Table 2 oeag060-T2:** End-points of the randomized controlled AFFELECT trial

Outcome measure	
PRIMARY OUTCOME	
Sinus rhythm	Prevalence of sinus rhythm in the treatment arms measured by electrocardiography at 1 month. The ECG is taken on a prespecified day aiming for the closest working day 4 weeks after the outpatient clinic visit (4–5 weeks after original ED visit).
SECONDARY OUTCOMES	
Number of cardioversions	First week after randomization (before preplanned outpatient clinic visit) One month after out-patient clinic (before control ECG) Overall (from randomization to 1 month control ECG)
Unplanned CVs in delayed cardioversion group	The number of subjects needing unplanned cardioversion before preplanned outpatient clinic visit (within four days after randomization) due to medical reasons or due to subjectively perceived unbearable symptoms (EHRA III or IV).

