New initiation of antiarrhythmic drugs (AAD)	Unplanned initiation of AADs at any point during the first month First week after randomization (before preplanned out-patient clinic) One month after outpatient clinic (before control ECG) Overall (from randomization to 1 month control ECG)
Proportion of patients with significant change in treatment strategy	The proportion of patients in whom the treatment strategy is changed from rhythm control to rate control due to low symptom burden, as evaluated at first cardiology outpatient clinic visit in accordance with ESC guidelines.
Hospitalization due to cardiovascular causes^a^	First week after randomization (before preplanned out-patient clinic) One month after outpatient clinic (before control ECG)
Quality of life	Quality of life as assessed by standardized questionnaires (AFEQT, EHRA-scale) First week after randomization (before preplanned out-patient clinic) One month after outpatient clinic (before control ECG)

^a^Serious adverse events are screened for during the first month of the study (before control ECG). Serious adverse events include thromboembolic events (ischaemic strokes and other thromboembolic events), hospitalization for decompensated heart failure or for serious arrhythmic events (sudden cardiac death or events leading to cardiopulmonary resuscitation) and hospitalization due to any cardiovascular complication or disease.

In addition, end-points are evaluated at 3 months and 5 years after the clinic visit, including recurrence of atrial arrhythmias at both time points and incidence of permanent AF/AFL at 5 years. Symptom severity is assessed up to one month, but not at 5 years.

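### SAE screening stops at the control ECG, which leaves a cardioversion deferred for thrombus at most 7 days of screening; the planned 3-month review should be used for a stated SAE comparison

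*Protocol article*

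**What the plan says.** All places are in the Protocol article.

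- **SAE window** (Primary and secondary end-points, Table 2, footnote a): "Serious adverse events are screened for during the first month of the study (before control ECG"). The same footnote defines the events: "Serious adverse events include thromboembolic events (ischaemic strokes and other thromboembolic events"), together with cardiovascular hospitalizations and serious arrhythmic events.
- **Clinic visit** (Patient management in both groups): "All patients visit cardiological outpatient clinic within 5–9 days after discharge from ED".
- **Control ECG** (Data collection and follow-up): "a standard 12-lead ECG is recorded for all patients after 4 weeks (closest working day) from cardiology outpatient clinic visit". Table 2 places it at "4 weeks after the outpatient clinic visit (4–5 weeks after original ED visit").
- **Acute CV** (Patient eligibility): "If randomized to acute CV group, the procedure must be performed within 48 h of arrhythmia onset".
- **Delayed CV** (Patient management in both groups): done at the clinic visit if the arrhythmia has not converted by then. For a thrombus: "If a thrombus is found in TEE, CV is delayed for at least 3 weeks to ensure adequate anticoagulation", with a repeat TEE before the procedure.
- **Later data** (Data collection and follow-up): "All patient health records, and the Finnish Care Register for Healthcare are reviewed 1 and 3 months after the outpatient visit", and again at 1 and 5 years. Major adverse cardiac and cerebrovascular events are among the items recorded.
- **Later end-points** (text after Table 2): evaluation at 3 months and 5 years, naming arrhythmia recurrence and permanent AF/AFL but not SAEs.

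**The concern.** Thromboembolism around CV is the hazard the protocol takes most care to guard against, through TEE and anticoagulation before the procedure. The footnote ties the end of SAE screening to the clinic visit, not to the procedure. A CV done late in the delayed strategy may therefore have little or no screened time after it. The clearest case is the thrombus pathway. The article describes TEE only for CV in the delayed arm, so deferral for thrombus arises as a planned pathway in that arm alone.

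At stake is how well the trial can support the Discussion's proposal that rhythm control can be deferred safely. Thromboembolic events are likely to be few, and the Interim analysis section says that no independent safety board was set up. One or two events falling just outside the defined window could change how the safety comparison reads.

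**Working it through.** **Inputs.** Day 0 is the ED visit. Clinic visit on day c = 5 to 9. ECG 28 days after the visit. Acute CV on day a = 0 to 2 (the 48 h limit runs from onset, so day 2 is the latest). Elective delayed CV on day c. Thrombus-deferred CV at least 21 days after the clinic TEE. Discharge is taken as the day of the ED visit, because patients who need more than 24 h in hospital are excluded. The closest-working-day rule is ignored: 28 days after a weekday is the same weekday, so only public holidays would shift it.

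**Step 1: the plan's own timing.** ECG day = c + 28 = 33 to 37, or 33/7 = 4.7 to 37/7 = 5.3 weeks. This agrees with Table 2's 4–5 weeks apart from a slight overrun at the top. It is the same for both arms, because both have the day 5–9 visit.

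**Step 2: screened time after CV under the footnote.**

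| CV | Day of CV | Days to control ECG |
|---|---|---|
| Acute, in the ED | 0 to 2 | 33 − 2 = 31 to 37 − 0 = 37 |
| Delayed arm, unplanned early | 0 to 4 | 33 − 4 = 29 to 37 − 0 = 37 |
| Delayed arm, elective at clinic | c | (c + 28) − c = 28 |
| Delayed arm, deferred for thrombus at clinic TEE | c + 21 or later (26 to 30 at the earliest) | at most (c + 28) − (c + 21) = 7 |

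For the same clinic day, elective CV has c − a = 3 to 9 fewer days than acute CV (3/31 = 10% to 9/37 = 24%). For thrombus patients the 3 weeks is a minimum. If CV takes place more than 28 days after the visit, none of the time after it is screened.

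The thrombus rule is written for CV at the clinic visit. If it were also applied to a TEE at an unplanned early CV (day 0–4), CV would come on day 21–25 at the earliest. That leaves at most 33 − 25 = 8 to 37 − 21 = 16 days.

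**Step 3: the same quantities up to the 3-month review** (taking 3 months as 91 days after the visit). Acute: 96 − 2 = 94 to 100 − 0 = 100 days. Elective delayed: 91 days. Thrombus-deferred: at most 91 − 21 = 70 days.

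**The case against.** The strongest reply is that follow-up is equal where it matters. The trial compares randomized strategies by intention to treat. Both arms are screened from randomization to day 33–37. The delayed arm's wait in arrhythmia, including at least 3 weeks of waiting with a known thrombus, lies inside that window. The date of CV is a post-randomization event that spontaneous converters do not have, so it cannot serve as time zero. This stands. A reader might infer that the window under-counts the delayed arm's events by its very construction; with equal windows from randomization, the documents do not support that.

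A second reply is that later events are not lost. Records and the register are reviewed in all patients at 3 months, 1 year and 5 years. The Interim analysis section describes continuous SAE monitoring with no stated end, and the list of later end-points is not worded as exhaustive. This also stands as to collection: it would be wrong to say that events are counted only to 1 month. It does not supply a comparison. The one SAE window the article defines ends at the ECG, and nothing says that the 3-month data enter a between-arm SAE analysis. Because the window is stated, this is more than a detail left to a fuller document.

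Third, the 28-day figure concerns only patients cardioverted at the clinic. It does not apply to spontaneous converters, and early unplanned CV has 29–37 days. Nothing in the documents shows that 28 days is too short. This stands too, and it is why the weight rests on the thrombus pathway.

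Finally, a reader might take the footnote's first month as a literal 30 days and get still shorter windows. The footnote's own parenthesis names the control ECG as the end, so that reading is not supported.

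**Conclusion.** The point holds in a narrow form. The defined SAE window is fair as a comparison from randomization, but it can close within 7 days of a thrombus-deferred CV, or before it. For elective clinic CV the shortfall is 3–9 days against acute CV, which is minor by itself.

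The result rests on the article's stated timings, on acute CV by day 2, and on the thrombus being found at the clinic-visit TEE. How many patients are affected cannot be computed, because the documents give neither the number of TEEs nor the rate of thrombus. That TEE is described only for the delayed arm shows where thrombus is looked for, not that it is absent in the other arm. The primary end-point is not affected. This is a low-cost improvement to the safety definition, not evidence of a biased safety comparison.

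**What to change.** In Table 2 and the analysis plan:

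1. Keep randomization as time zero for all SAE comparisons.
2. State that SAEs, thromboembolic events above all, are also compared between the randomized arms up to the 3-month record and register review.
3. Keep the count up to the control ECG as an additional window.
4. List any SAE after a thrombus-deferred CV individually, with days since CV, and report how many patients had such a deferral.

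The cost is wording only, because the 3-month review is already planned; no visit or treatment rule changes. The drawback is that some late events unrelated to CV will enter the count, which is one reason to keep the earlier window beside it. The extension does not make time after CV equal across pathways. It makes that time long enough, up to about 70 days for a thrombus-deferred CV done at the earliest date, for the safety comparison to include what follows the strategy's last procedures.

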### Rhythm control and anticoagulation strategy in the acute rhythm control group

Patients randomized to acute rhythm control undergo CV in the ED. Electrical and medical CV are both viable options in the study, and the decision is made by the treating physician. If the first method fails (for example pharmacological CV), another can be adopted. Anticoagulation is initiated in accordance with the ESC guidelines.^9^ Patients are followed up and discharged from the ED following the standard procedure. All participating patients are scheduled an appointment at a cardiologic outpatient clinic within 5–9 days after the ED visit. The appointment time is scheduled before discharge or, at the latest, on the following working day.

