### Rhythm control and anticoagulation strategy in the delayed rhythm control group

Patients randomized to delayed rhythm control are discharged immediately after their anticoagulation status has been secured and adequate rate control (heart rate <110 bpm) is ensured. The effectiveness of pre-existing anticoagulation therapy is verified (adherence to the use of direct oral anticoagulants [DOACs] or by verifying INR values for warfarin users) and patients with no prior anticoagulation are initiated on a DOAC regardless of the CHA_2_DS_2_-VASc score. However, if a patient experiences spontaneous return to SR before discharge and has very low thromboembolic risk (CHA2DS2-VASc = 0), no anticoagulation is initiated. Before discharge from the ED, or at latest the following working day, patients are scheduled for an appointment at a cardiologic outpatient clinic within 5–9 days, which includes the delayed (elective) CV. If the patient feels that the rhythm has spontaneously restored to SR before the planned CV, an ECG is taken to confirm this event on the next working day, at the latest.

The patient is referred to acute CV in the ED as soon as possible (with a transoesophageal echocardiography [TEE] guided CV for patients without previous anticoagulation therapy for at least 3 weeks, which has been shown to be safe^21,22^) if the patient randomized to delayed rhythm strategy feels that a more expedient CV is called for due to unbearable symptoms. All patients without previous anticoagulation for at least 3 weeks are advised of this option before consenting to the trial, including the possibility of TEE-guided CV. Patients also have the option to consult research personnel during office hours or go to the ED if the symptoms are unbearable during night-time or during weekend.

Patients are advised to seek acute medical care directly if they suspect that AF or AFL has recurred, or if they otherwise require urgent evaluation and/or care, regardless of whether study personnel have been contacted. This recommendation applies from discharge from the ED up until the first-month ECG control. If arrhythmia symptoms persist for a few hours and AF or AFL is recorded, the patient is referred to ED for implementation of acute rhythm control. If rate control is selected as the preferred strategy by the treating cardiologist at any point in the study, the ECG is, nevertheless, recorded at the earliest possible opportunity.

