### Interim analysis

The AFFELECT trial is deemed a low-risk trial and no independent safety monitoring board was established based on prior evaluation and ethical committee decision. However, continuous monitoring for serious adverse events (thromboembolic events and hospitalizations due to heart failure) is applied.

A statistical interim analysis for serious safety events was performed in March of 2023 by an independent statistician from Tampere University, 5 weeks after the randomization and obtaining first month follow-up data of 200 patients comparing the risk of cardiovascular hospitalizations blinded to the group allocation. No statistically significant association was found, and the study was continued as planned.

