## Discussion

Early CV in the ED has long been the standard approach to managing recent-onset AF/AFL. However, given the high recurrence rate of AF and the growing number of affected patients, this strategy places a significant burden on emergency services, where resources are often stretched and patient turnover is high.^1–3,5^ The AFFELECT trial introduces a novel approach to the management of acute AF/AFL by challenging the long-standing practice of immediate rhythm control in the ED.

The AFFELECT trial proposes that rhythm control can be safely deferred for 5–9 days in clinically stable patients, shifting care from the ED to elective cardiology units. This approach allows for spontaneous conversion in many cases^16^ and facilitates a more measured, patient-centred decision-making process regarding CV. The clinical comparison focuses on overall sinus rhythm prevalence at 4 weeks and the total number of CV procedures required to achieve this outcome in each strategy. This reflects the real-world decision faced in the ED and promotes a more individualized, resource-conscious, and clinically deliberate pathway that better aligns with practical clinical management.

Treating haemodynamically stable patients in dedicated elective cardiology units rather than crowded EDs could offer several advantages. It may substantially reduce the number of CVs performed, lower healthcare costs, and prevent repeated unnecessary ED visits. Moreover, concentrating the management of these patients in specialized cardiology settings enables more structured follow-up, coordinated decision-making, and comprehensive rhythm control strategies, which are associated with a reduction of morbidity and mortality in selected patients.^26^ If successful, this paradigm could meaningfully redefine the standard of care for acute AF/AFL, aligning patient safety, clinical efficiency, and sustainable healthcare delivery.

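### The stated safety outcomes count embolism but name neither bleeding nor all-cause death, although the anticoagulation rules are written differently by arm

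*Protocol article*

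**What the plan says.** Safety events are described in two sections of the protocol article.

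- Primary and secondary end-points: the main text lists cardiovascular events, including those monitored for safety, as a secondary end-point. Footnote a to Table 2, attached to the row on cardiovascular hospitalization, spells this out: "Serious adverse events include thromboembolic events (ischaemic strokes and other thromboembolic events), hospitalization for decompensated heart failure or for serious arrhythmic events". It explains the arrhythmic events as sudden cardiac death or resuscitation, and adds "hospitalization due to any cardiovascular complication or disease".
- Interim analysis: continuous monitoring covers thromboembolic events and heart-failure hospitalizations. A comparison of cardiovascular hospitalizations in 200 patients was made in March 2023, with the outcome "No statistically significant association was found, and the study was continued as planned". No counts, estimate or interval are given.

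Anticoagulation is described separately by arm. In the delayed group, "patients with no prior anticoagulation are initiated on a DOAC regardless of the" CHA2DS2-VASc score. There is one exception: "if a patient experiences spontaneous return to SR before discharge and has very low thromboembolic risk" (score 0), none is started. For the acute group the text is "Anticoagulation is initiated in accordance with the ESC guidelines".

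The Discussion says the trial proposes that "rhythm control can be safely deferred for 5–9 days in clinically stable patients".

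**The concern.** The benefit expected of anticoagulation is fewer emboli and its main harm is bleeding. If the arms differ in who is anticoagulated, a safety comparison needs both. As written, embolism is counted and bleeding is not, so any excess bleeding under the delayed strategy would not appear in a planned safety comparison. Deaths other than sudden cardiac death are likewise not named.

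The interim adds to this. A non-significant test with no counts or interval does not tell the reader which differences were excluded, and with no independent safety board it is the only formal safety comparison described so far. At stake is what the trial can say about the safety of deferral. The primary comparison of sinus rhythm is not affected.

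**Working it through.** **1. The safety lists side by side**

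| Where | What is named | Bleeding | All-cause death |
|---|---|---|---|
| End-points, main text | Cardiovascular events, including those monitored for safety | Not named | Not named |
| Table 2, footnote a | Thromboembolism, heart-failure admission, serious arrhythmic events, other cardiovascular admission | Not named | Sudden cardiac death only |
| Interim analysis, continuous monitoring | Thromboembolism, heart-failure admission | Not named | Not named |
| Interim analysis, 200 patients | Cardiovascular hospitalization | Not named | Not named |

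Bleeding appears only in Table 1, as an example under the exclusion for patients who cannot safely be anticoagulated. The catch-all in footnote a covers cardiovascular admissions. It does not clearly reach a gastrointestinal bleed, or any bleed managed without admission.

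**2. The anticoagulation rules side by side**

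The delayed arm has an explicit rule that overrides the stroke-risk score, with one exception. The acute arm has a reference to an outside guideline. The wording differs. Whether exposure differs, and by how much, depends on a source that is not part of the document.

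**3. The plan's own figures**

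The only power calculation concerns sinus rhythm, and it reproduces: 2 × 0.9 × 0.1 × (1.96 + 1.2816)² / 0.10² = 189.1, so 190 per group and 380 in total. Then 190 / (1 − 1/3) = 285, 190 + 285 = 475, and 475 + 25 = 500. No event rate, detectable difference or power is stated for any safety outcome.

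**4. Power of the interim comparison**

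Inputs: 200 patients (Interim analysis) and allocation 2:3 (Randomization), hence about 80 acute and 120 delayed. That split, a two-sided 5% test and the event rates are assumptions.

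Power = Φ[(p₂ − p₁ − 1.96 × SE₀) / SE₁], where SE₀ = √[p̄(1 − p̄)(1/80 + 1/120)], p̄ = (80p₁ + 120p₂)/200, and SE₁ = √[p₁(1 − p₁)/80 + p₂(1 − p₂)/120].

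For 2% vs 4%: p̄ = 0.032, SE₀ = 0.0254, SE₁ = 0.0238. Then (0.02 − 0.0498)/0.0238 = −1.25, which gives a power of 11%.

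| Acute vs delayed (doubling) | Interim, 80 vs 120 | Full trial, 200 vs 300 |
|---|---|---|
| 2% vs 4% | 11% | 22% |
| 3% vs 6% | 15% | 33% |
| 5% vs 10% | 23% | 53% |
| 8% vs 16% | 37% | 76% |
| 10% vs 20% | 47% | 86% |

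Enumerating both binomials at the interim sizes gives 9%, 15%, 24%, 38% and 48% for the uncorrected χ² test, and 5%, 9%, 20%, 35% and 44% for Fisher's test. For 80% power the true interim rates would have to be about 3% vs 14.7%, or 5% vs 18.1%. For a tripling, power is higher: 25% at 2% vs 6%, 38% at 3% vs 9%, and 61% at 5% vs 15%.

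**5. What an interval would show**

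At a common rate of 3%, the approximate 95% half-width is 1.96 × √[0.03 × 0.97 × (1/80 + 1/120)] = 4.8 percentage points at the interim. With 200 and 300 patients it is 3.1 points. If no events occurred, the upper 97.5% bound is 1 − 0.025^(1/120) = 3.0% for 120 delayed patients and 1 − 0.025^(1/300) = 1.2% for 300.

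**6. How many bleeds might be involved**

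Assume that half of the 300 delayed patients start a DOAC and that 0.5% to 2% have a clinically relevant bleed in about five weeks. Then 150 × 0.005 to 150 × 0.02 = 0.75 to 3 events. Both inputs are assumptions. The result counts all bleeds in those patients and not the excess over the acute arm.

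**The case against.** The strongest defence is that this is a condensed article and the footnote says the events *include* those listed, so the full protocol may define bleeding. Data collection and follow-up also records all specialized-care visits and major cardiac and cerebrovascular events from health records and the national register, so a bleed treated there is in the data. Table 1 excludes patients with a history of severe bleeding. The guideline followed in the acute arm may lead to similar anticoagulation, so a difference in exposure is not established.

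Much of this stands, and it limits the point. But the lists positively state what is counted, and an event that can be found in the records is not thereby a named outcome compared between arms.

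A reader might also infer stronger claims, which the document does not support:

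- That every previously untreated delayed-arm patient starts a DOAC. The exception for sinus rhythm before discharge with score 0 rules this out.
- That interim power was below 25%. For a doubling this needs an acute-arm rate of about 5% or less, and no rate is stated.
- That the interim ignored embolism. Footnote a places thromboembolic events under cardiovascular hospitalization, so admitted strokes were plausibly included.
- That the claim of safe deferral rests on the interim and so cannot be supported. The Discussion words it as a proposal, the interim served only to continue the trial, and the final safety data come from all patients.
- That complications of the additional transoesophageal echocardiography go unrecorded. Patient management in both groups says complications are recorded with the cardioversion data.

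**Conclusion.** The concern holds in a limited form. Bleeding and all-cause death are not named in any stated safety list, while the anticoagulation rules are worded differently by arm, so the safety comparison as described is one-sided. The size of any difference in exposure cannot be determined from the article, and the number of bleeds is probably small.

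The interim result is weak reassurance: about 11% to 47% power for a doubling, given assumed acute-arm rates of 2% to 10%, an 80 to 120 split and a two-sided 5% test. Even the full trial reaches only 22% to 53% for a doubling from 2% to 5%. Final safety results therefore also need intervals and cannot rest on significance tests alone. This is an inexpensive improvement to what the trial can say about safety. It does not bear on the non-inferiority conclusion or on which anticoagulation rule is appropriate.

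**What to change.** Name major bleeding, clinically relevant bleeding and all-cause death as safety outcomes in both arms, from randomization to the 1-month ECG, with a stated definition of each. Take them from the health records and care register already under review. Recruitment is described as ongoing, so this can be fixed before the comparative analysis.

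Report every safety outcome as counts by arm and a risk difference with an exact or score 95% confidence interval, and not by significance test alone. Report the 2023 interim in the same way, and do not offer its non-significance as evidence of safety.

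The cost is a few more events to code and some added wording; no new data source and no change to treatment is needed. The drawback is that the intervals will be wide, so the safety statement will be more modest.
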